- **Study Protocol**
- **Effectiveness of Reciproc system for anterior teeth with apical periodontitis: a randomized controlled pragmatic trial**
- **Proponent:**
- PhD Student: [name]
- Health Sciences Graduate Program
- Federal University of Sergipe
- **Doctoral Adviser:**
- [name]. [name]
- Department of Dentistry
- Health Campus / Biology and Health Science Center
- Federal University of Sergipe
- Aracaju
- June 2015
- **ABSTRACT**
- Single file canal preparation techniques emerged in an attempt to overcome drawbacks related to manual and continuous rotary techniques. It has shown promising results in in-vitro studies, but its effectiveness has not yet been tested in clinical studies. Hence, this proposal seeks to investigate, through an equivalency randomized controlled clinical trial, the effectiveness of the Reciproc® single file, single cone system, regarding its success rate, incidence rate of post-operative pain and PAI score changes. This trial will follow the Consort guidelines, having a parallel design and using an active treatment as control – the crown-down instrumentation technique and the lateral condensation obturation technique. Patients in need of endodontic treatment for anterior teeth due to pulp necrosis and with radiographic evidence of apical periodontitis will be randomized to receive endodontic treatment either by the Reciproc® single file, single cone system or by the crown-down manual technique with stainless steel files. Patients will be questioned about their pain levels at baseline and then 24 hours, 72 hours days and 7 days after treatment is performed. The Wilcoxon test will be used to compare treatment pain scores. Patients will be called for one- year follow-up visits in which PAI score changes and clinical signs of periapical pathosis will be ascertained. Data related to PAI scores will be submitted to the Wilcoxon test to compare treatment outcomes and to the Man-Whitney test to compare one-year follow-up scores within each treatment group. Each individual treatment will be classified as “success” if their PAI scores are 2 or lower and they show no clinical signs or symptoms of periapical disease. Success rates of each treatment and the relative risk of experimental group in relation to control will be determined. In addition, Fishers exact test will be used to compare treatment groups’ success rates. For all analyses, a 95% significance level will be used.

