- Therefore, the research question is the following: For patients presenting anterior teeth with pulp necrosis and apical periodontitis, is there difference in the outcomes obtained with hand file instrumentation and lateral compaction obturation compared with the outcomes obtained with reciprocating single file instrumentation and single cone obturation, concerning the healing of periapical lesions and postoperative pain incidence and severity? The hypothesis to be tested is that using reciprocating single files instrumentation and single cone obturation has similar effectiveness treating apical periodontitis as hand file instrumentation and lateral compaction obturation technique. In addition, the hypothesis that both endodontic protocols result in the same incidence and severity of postoperative pain and flair-up will also be tested.
- 5.2 Method
- 5.2.1 Sample Size Calculation
- The sample size was calculated for the main outcome, defined as the mean periapical index score (PAI) difference between protocols of the apical lesion 1 year after treatment. The calculation for similarity trial used an equivalence limit of 0.5, a standard deviation of 0.74 (20), type I error of 0.05, and a power test of 0.90. Furthermore, the sample was increased by 20% to compensate for any drop-out. This resulted in 60 teeth per experimental condition.
- 5.2.2 Recruitment and eligibility criteria
- The recruited participants will be patients who are scheduled for an endodontic treatment in one of the public services where the study will take place. Patients with anterior teeth presenting pulp necrosis and radiographic evidence of apical periodontitis (symptomatic apical periodontitis, asymptomatic apical periodontitis, and chronic apical abscess) with a diameter greater than 2 mm will be invited to participate in the study. Those who agreed to participate and sign the informed consent (appendix I) form will be included in this study. Only one tooth per participant will be included in the trial. Teeth with an immature apex, any radiographic evidence of root resorption, previously treated root canal or requiring extensive prosthetic rehabilitation will be excluded. Participants presenting a pre-existing health or oral condition that placed them at risk during the trial, as well as those having generalized periodontal disease, and women who are pregnant or breastfeeding are also going to be excluded.
- 5.2.3 Baseline evaluation

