- Baseline demographic data of the participants and clinical characteristics of the teeth included in the study will be categorized, and the absolute and relative frequencies calculated (except for PAI scores, final preparation size scores, age and follow-up time). The difference between the interventions regarding the distribution of these characteristics will be assessed by Chi-squared analysis. For PAI scores, final preparation size scores, age and follow-up time, data will be analyzed using either t-test or Mann-Whitney Rank-Sum test.
- The Wilcoxon Rank-Sum test for equivalence using two one-sided tests (TOST) procedure will be used to assess if, 12 months after the treatment, the 95% confidence intervals of the mean PAI score treatment difference falls within the pre-established equivalence limit (main outcome of interest). For all other outcomes, traditional two-sided superiority analyses will be used. The association between treatment protocol and changes on periapical status will be analyzed by Chi-squared test or by Fisher`s exact test. The success rates for each treatment protocol will be calculated, and differences analyzed by Chi-squared testing. Univariate logistic regression will used to determine any association between explanatory variables and the treatment’s success rate. Factors with a p-value < 0.1 will be included in a multivariate analysis. Odds ratios and 95% confidence intervals will be calculated.
- For all VAS data, normal distribution and possible differences between the treatments will be assessed through the Shapiro-Wilk test and t-test, respectively. Data from VRS will be analyzed through the Wilcoxon rank-sum test. The incidence of postoperative pain and flare-up will be calculated, and Chi-squared tests will be used to assess any possible association between treatment and incidence. Differences between the treatments regarding the incidence and intensity of postoperative pain will be calculated, as well as their confidence intervals at 95%. The level of significance will be set at 95% for all analyses.
- .
- **6. Scientific contributions of the proposal**

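### Section 5.3 selects the terms of the multivariable success model by univariate p < 0.1, without keeping treatment in or limiting candidates to baseline variables

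*Protocol*

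**What the plan says.** Section 5.3 treats success in two steps. The first is the comparison between arms: "The success rates for each treatment protocol will be calculated, and differences analyzed by Chi-squared testing". The abstract adds Fisher's exact test and a relative risk: "Success rates of each treatment and the relative risk of experimental group in relation to control will be determined".

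The second step is a regression: "Univariate logistic regression will used to determine any association between explanatory variables and the treatment’s success rate". The selection rule comes next: "Factors with a p-value < 0.1 will be included in a multivariate analysis". Odds ratios and 95% confidence intervals are then promised. The explanatory variables are not named. Nothing says whether treatment is one of them, whether it stays in regardless of its p-value, or whether the search is exploratory.

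Final preparation size appears earlier in the same section, among the characteristics compared between arms: "For PAI scores, final preparation size scores, age and follow-up time, data will be analyzed using either t-test or Mann-Whitney Rank-Sum test".

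Two further statements matter. The hypothesis in section 5.1 is that the experimental protocol "has similar effectiveness treating apical periodontitis as hand file instrumentation and lateral compaction obturation technique". Section 5.3 also says of everything except the primary outcome: "For all other outcomes, traditional two-sided superiority analyses will be used".

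**The concern.** A univariate p-value screen lets the trial's own small data set choose the model. Three things can go wrong.

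- **Treatment can fall out.** If treatment is screened with the rest, a trial that expects similar arms will usually remove its own randomised factor.
- **A consequence of treatment can come in.** Under section 5.2.4 the envelope is opened only at the intervention. Under section 5.2.6 the final size then follows a different rule in each arm: a set number of sizes above the first file used for hand files, and a choice of R25, R40 or R50 for Reciproc. Final size is therefore a post-randomisation variable set by the technique. Conditioning on it removes whatever part of the treatment effect acts through it.
- **The intervals ignore the selection.** With few failures, which factors pass is partly chance, and the reported intervals treat the chosen model as if it had been fixed in advance.

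Success is specific objective 2. Section 5.3 promises no other interval estimate for success than these odds ratios, so readers may well take them as the adjusted result.

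**Working it through.** **Size of the data set.** Section 5.2.1 gives a margin of 0.5, SD 0.74, type I error 0.05, power 0.90 and a 20% increase for drop-out. For equivalence of means by two one-sided tests:

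n = 2 × [0.74 × (1.645 + 1.645) / 0.5]² = 47.4, so 48 per arm; 48 / 0.80 = 60.

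The stated 60 per arm is reproduced. If the full 20% is lost, 48 per arm (96 teeth) remain for the success analysis.

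**Number of failures.** The protocol gives no success rate by arm, so these rates are assumptions: 80% success gives 96 × 0.20 = 19 failures; 90% gives 96 × 0.10 = 10; 93%, the figure section 1.2 cites from an uncontrolled three-year study, gives 96 × 0.07 = 7.

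**Chance that treatment passes the screen, if it is screened.** Let a and b be the successes in two arms of n = 48. Treatment passes when its univariate test statistic exceeds 1.645²:

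- Likelihood ratio: 2[l(a,n) + l(b,n) − l(a+b,2n)], with l(k,m) = k ln(k/m) + (m−k) ln(1−k/m).
- Wald: (difference in log-odds)² / [1/a + 1/(n−a) + 1/b + 1/(n−b)].

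Summing the exact binomial probabilities over all (a, b) gives the following ranges across the two tests:

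| Assumed true success | Passes | Dropped |
|---|---|---|
| 70% v 70% | 10% | 90% |
| 80% v 80% | 10-11% | 89-90% |
| 90% v 90% | 8-11% | 89-92% |
| 93% v 93% | 5-13% | 87-95% |
| 80% v 75% | 16% | 84% |
| 80% v 70% | 31% | 69% |
| 90% v 80% | 38-41% | 59-62% |
| 93% v 83% | 41-46% | 54-59% |
| 80% v 65% | 50% | 50% |
| 80% v 60% | 70% | 30% |
| 90% v 70% | 80-82% | 18-20% |

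Hand check for 80% v 70%: SE = √[(0.16 + 0.21)/48] = 0.088; 0.10/0.088 = 1.14; Φ(1.14 − 1.645) ≈ 0.31. With no drop-out (60 per arm), treatment passes in 6-12% of trials with equal rates and 35-36% at 80% v 70%.

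**Entry of final preparation size.** Four scenarios were simulated (4,000 trials each, 48 per arm, success about 80%). All inputs are assumed: size differs between arms by 0.5 or 1 SD, size has a log odds ratio of 0.5 or 0.8 per SD, and the whole treatment effect acts through size.

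| Shift (SD) | Log-OR per SD | Size enters | Size enters, treatment does not | Median treatment log-OR, unadjusted | With size also fitted |
|---|---|---|---|---|---|
| 0.5 | 0.5 | 63% | 54% | 0.24 | about 0 |
| 0.5 | 0.8 | 93% | 76% | 0.37 | about 0 |
| 1.0 | 0.5 | 68% | 47% | 0.48 | about 0 |
| 1.0 | 0.8 | 96% | 53% | 0.73 | about 0 |

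This is the extreme case of full mediation. With partial mediation only part of the effect would be absorbed.

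**Effect of the selection.** In the same simulations, among trials where treatment passed, its median unadjusted log odds ratio was 1.05-1.16, against 0.24-0.73 over all trials. Separately, k independent factors with no effect yield at least one false entry with probability 1 − 0.9^k: 41% for k = 5 and 65% for k = 10. The value of k is assumed, since the candidates are not named.

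**The case against.** The strongest reply is that the regression is a search for prognostic factors and is never offered as the treatment comparison. That stands. The randomised comparison of success is the Chi-squared test in section 5.3 (Fisher's exact test and relative risk in the abstract). It is valid under randomisation and untouched by the screen. A reader might infer that the plan leaves success without a valid treatment comparison, or that it promises an adjusted effect and fails to deliver one. The documents support neither.

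Other limits also stand:

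- Final preparation size is listed for comparison between arms and is not named as a model candidate. Its entry is possible, not planned. It is a plausible candidate, because the randomised trial that supplies the SD in section 5.2.1 is, by its title, about apical preparation size and outcome. In a purely prognostic analysis it would be a reasonable factor to examine.
- Follow-up time is also measured after randomisation, but all patients are called at 12 months and nothing in the protocol suggests that technique determines it. No bias from it is shown.
- A flat statement that treatment will usually be dropped goes too far. It requires that treatment is screened and that the true difference is no more than about 10 points; at 15-20 points treatment passes in half or more of trials.
- How much too narrow the intervals would be was not computed.

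The reply that the details belong in an analysis plan answers only part of the point. A candidate list may sit there, but the protocol itself fixes the p < 0.1 rule, and that rule is what is faulted.

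**Conclusion.** The point holds as a poorly chosen model-building rule for a secondary outcome. As written, the rule protects neither treatment nor a baseline-only set of covariates. If treatment is screened, it leaves the model in 87-95% of trials with truly equal arms, and in about 60-70% at 80% v 70% or 90% v 80% (slightly less, 54-59%, at 93% v 83%). These figures assume 48 evaluable teeth per arm and success rates that the protocol does not give. If final preparation size enters alongside treatment, the treatment odds ratio no longer measures the total effect of the technique. The loss depends on how far the effect acts through size and reaches the whole effect only under full mediation. With roughly 7-19 failures, the selected factors would be unstable and their intervals would not reflect the selection.

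The primary equivalence analysis, the sample size and the unadjusted comparison of success need no change. The point is worth acting on because it concerns a stated objective and the correction is cheap, but it does not threaten the main conclusion of the trial.

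**What to change.** In section 5.3, replace the screening rule with three statements:

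1. Success will be analysed with one pre-specified logistic model that always contains treatment and baseline PAI, reported with odds ratios and 95% confidence intervals alongside the existing unadjusted comparison.
2. Final preparation size, being set by the allocated technique, will not be included in any model that reports a treatment odds ratio.
3. Any wider search for factors associated with success is exploratory and will be labelled so.

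Baseline PAI is already recorded under section 5.2.3, so no new data, sample size change or change of conduct is needed. The downside is that fewer factors are examined in the reported model. If failures are as few as about 7, even two terms are demanding, and the unadjusted comparison should carry the most weight.

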- **Key Words:** Periapical Periodontitis; Root Canal therapy; Randomized Controlled Clinical Trial
- **RESUMO**
- A técnica de instrumentação de canais radiculares com único instrumento reciprocante surgiu como uma tentativa de superar as limitações apresentadas pelas técnicas manuais e de rotação continua. Apesar da facilidade técnica, poucos estudos avaliaram a efetividade do uso de instrumentação reciprocante na prática clínica. Assim, o objetivo desta proposta será avaliar o desempenho clínico da instrumentação reciprocante e obturação com cone único do sistema Reciproc®, no que concerne ao índice de sucesso do tratamento endodôntico e à incidência de dor pós-operatória, através de um ensaio clínico randomizado controlado. Este será realizado seguindo as recomendações do *Consort*, usando controle ativo – instrumentação manual pela técnica coroa-ápice e obturação pela técnica da condensação lateral. Pacientes que apresentem dentes anteriores com quadro clínico de necrose pulpar e evidência radiográfica de periodontite apical serão randomizados para tratamento endodôntico com limas do sistema Reciproc® ou para tratamento com limas manuais. O paciente será questionado qual seu nível de dor percebida antes de iniciar o tratamento e 24 horas, 72 horas e 7 dias após sua realização; os escores serão submetidos ao teste de Wilcoxon para comparação das técnicas endodônticas. Doze meses após o tratamento, os pacientes serão convocados para nova avaliação clinica e radiográfica, na qual serão verificadas alterações no índice PAI com relação ao registrado no *baseline* e sinais ou sintomas clínicos de periodontite periapical. Os dados relativos ao índice PAI serão submetidos ao teste de Wilcoxon para comparação entre as técnicas e ao teste de Man-Whitney para comparar os scores observados na avaliação de 12 meses. O sucesso de cada tratamento será caracterizado se o dente apresentar índice PAI igual ou inferior a 2 e na ausência de sintomatologia clínica. As percentagens de sucesso de cada tratamento e o risco relativo do tratamento experimental em relação ao controle serão calculados. Além disso, as percentagens de sucesso de cada tratamento serão comparadas pelo teste exato de Fisher. Para todas as análises, será utilizado nível de significância estatística de 95%.
- **Palavras-chave:** Periodontite Periapical; Preparo de Canal Radicular; Ensaio Clínico
- **1. Introduction**
- 1.1 Research problem

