5. Enhance the quality of education provided to students of the graduate program in Health Sciences of the Federal University of Sergipe;
6. Produce a doctoral thesis and at least two original research articles to be published in journals with an impact factor of 2 or more.
7. **Methodology**

- 5.1 Experimental Design
- This study will be a randomized controlled pragmatic clinical trial, which will follow the CONSORT (<http://www.consort-statement.org/>) statement guidelines. It will have a two-arm, parallel design (1:1 allocation ratio equivalency). The endodontic treatments to be performed are either a combination of a single-file and single-cone (SFSC) technique using the Reciproc system (experimental group) or an association of the crown-down hand files with the lateral compaction obturation (HFLC) technique (control group). The main outcome of interest is mean periapical index score (PAI) (19) difference between the two groups 12 months after treatment. Peak of pain during the first 24 hours after treatment and postoperative pain 24, 48 hours and 7 days after treatment are the secondary outcomes.
- The trial will be based on the following PICO question:
- P (Population): patients above 18 years of age, who are scheduled for an endodontic treatment in one of the public services where the study was performed cities (i.e., Capela, Estância, Laranjeiras and Nossa Senhora do Socorro) located in the state of Sergipe (Brazil), with anterior teeth presenting pulp necrosis and radiographic evidence of apical periodontitis (symptomatic apical periodontitis, asymptomatic apical periodontitis, and chronic apical abscess) with a diameter greater than 2 mm.
- I (Intervention): A combination of a reciprocating single-file and single-cone technique using the Reciproc system.
- C (Control): An association of the crown-down technique hand files with the lateral compaction obturation technique.
- O (Outcomes): Mean PAI difference between the intervention and the control group 12 months after treatment.

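### The protocol gives its decision threshold as a 95% level of significance where 5% is evidently meant, and leaves the per-side level of the primary equivalence test unstated

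*Protocol*

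**What the plan says.** The threshold appears three times in the protocol, each time as a significance level of 95%:

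- Section 5.3 (Statistical analysis), last sentence: "The level of significance will be set at 95% for all analyses".
- English abstract: "For all analyses, a 95% significance level will be used".
- Portuguese abstract (Resumo): "será utilizado nível de significância estatística de 95" per cent.

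Section 5.2.1 (Sample Size Calculation) plans the primary equivalence comparison with "type I error of 0.05, and a power test of 0.90". It does not say whether the 0.05 applies to each one-sided test.

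Section 5.3 judges the primary outcome by a rank-based TOST, asking whether "the 95% confidence intervals of the mean PAI score treatment difference falls within the pre-established equivalence limit". All other outcomes get two-sided superiority tests. Section 5.3 names 95% intervals in three places: for the PAI difference, the odds ratios and the pain differences. Its only explicit p-value cut-off is 0.1, for admitting factors to the multivariable model.

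**The concern.** The level of significance is the probability of rejecting a true null hypothesis. Section 5.2.1 sets it at 0.05, while section 5.3 and both abstracts set it at 95%. The two statements cannot both be right. Because the error stands in two languages and in the operative statistics section, it is more than one mistyped figure.

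The sentence matters because nothing else in the protocol sets a p-value threshold for the superiority tests (healing class, success, VAS, VRS, pain incidence, flare-up). The 0.05 in section 5.2.1 is an input to the primary sample size only.

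The sentence also covers the primary TOST, since it applies to every analysis. For a two-sided superiority test, turning 95% into 5% settles the matter. For a TOST it does not: 0.05 on each side goes with a 90% interval, while a 95% interval goes with 0.025 on each side. A correction that only swaps 95% for 5% would leave the primary decision rule open.

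**Working it through.** **Inputs.** From section 5.2.1: "an equivalence limit of 0.5, a standard deviation of 0.74", type I error 0.05, power 0.90, and "the sample was increased by 20% to compensate for any drop-out", giving 60 teeth per arm. From section 5.1: 1:1 allocation. From section 5.3: the 95% interval rule. Assumptions added here: true difference 0 and a normal approximation for a difference in means.

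**1. Reproduce the 60 per arm.** For equivalence at zero true difference, n per arm = 2 × [SD × (z(1−α) + z(1−β/2)) / margin]².

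- With α = 0.05 per side and β = 0.10: 2 × [0.74 × (1.645 + 1.645) / 0.5]² = 47.4, so 48 evaluable.
- Allowing for 20% drop-out: 48 / 0.8 = 60, the stated figure. Multiplying instead gives 48 × 1.2 = 57.6, so 58.

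The design figure therefore follows from an alpha of 0.05.

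**2. Does the 60 fix the per-side level?** Not beyond doubt.

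| Per-side α | β | Evaluable per arm | Divided by 0.8 |
|---|---|---|---|
| 0.05 | split (z = 1.645) | 48 | 60 |
| 0.05 | not split (z = 1.282) | 38 | 48 |
| 0.025 | not split (z = 1.282) | 47 | 59 |
| 0.025 | split (z = 1.645) | 57 | 72 |

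The first row matches exactly and the third comes within one tooth. The third would be the wrong formula for 90% power at zero difference, since it delivers only about 2 × 0.90 − 1 = 0.80, but it cannot be ruled out as the calculation used.

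**3. Power under each reading, 48 evaluable per arm.** SE = 0.74 × √(2/48) = 0.151, and margin / SE = 3.310. Power = 2Φ(margin/SE − z(1−α)) − 1.

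- One-sided 0.05 (90% interval): 2Φ(3.310 − 1.645) − 1 = 0.904.
- One-sided 0.025 (95% interval): 2Φ(3.310 − 1.960) − 1 = 0.823.

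If all 60 per arm were evaluable, the same formula gives 0.960 and 0.918. The shortfall against 90% therefore appears once the planned drop-out occurs.

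**4. The superiority threshold taken literally.** A two-sided α of 0.95 puts the critical value at |z| = 0.063, so 95% of comparisons between identical treatments would be called significant. This shows that the wording is wrong; it is not a forecast of what the trial would do.

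**The case against.** The strongest reply is that no reader would be misled. Section 5.3 names 95% confidence intervals three times, the last in the sentence just before the disputed one. Section 5.2.1 gives 0.05. The other tests are described as traditional two-sided ones. A 0.1 entry screen would make no sense beside a 0.95 test threshold. The sample size reproduces with 0.05, and correcting the wording changes no design figure.

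For the superiority tests this reply stands, and it limits the weight of the point. A reader might infer from the literal sentence that the plan would run with a 95% type I error and call nearly any result significant. The documents do not support that: no rule of p < 0.95 is written anywhere, and everything around the sentence points to 5%.

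The reply does not reach two things. The stated threshold is still wrong in three places, with no correct p-value rule elsewhere to override it. And for the primary TOST the surrounding text does not settle the level: 0.05 without a stated side and a 95% interval are compatible with different tests.

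**Conclusion.** The point holds as a correction of wording with one substantive loose end. The protocol calls 95% the level of significance where it should say 5%, which contradicts its own type I error of 0.05. Intent is recoverable, the sample size stays at 48 evaluable and 60 enrolled per arm, and the effect on the superiority analyses is minor.

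The loose end is the primary test. Under the 95% interval rule, power at 48 evaluable per arm is about 82%, against the stated 90%. Those figures rest on SD 0.74, margin 0.5, zero true difference, the full 20% loss and a normal approximation to what is planned as a rank-based test. The 95% interval is not itself an error: it is the stricter rule, but it does not go with 90% power at this sample size.

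**What to change.** In section 5.3 and both abstracts (translated in the Resumo), replace the sentence with: *All superiority tests are two-sided at a significance level of 5% (p < 0.05), with 95% confidence intervals.*

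For the primary TOST, state the per-side level in sections 5.2.1 and 5.3 and make it agree with the interval, in one of two ways:

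- one-sided 0.05 for each test with a 90% interval, which keeps power at about 90% with 48 evaluable per arm; or
- the 95% interval as now written, named as one-sided 0.025, with power restated as about 82% at 48 evaluable per arm.

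The cost is one sentence in three places plus a clause on the TOST. Neither option changes recruitment, data collection or treatment. The choice should be recorded before outcome data are seen.
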